## Abstract

**Background:**

Physical inactivity and sedentary behavior are increasingly common problems in the general population, which can lead to overweight, obesity, diabetes, cardiovascular disease, and decreased motor and cognitive capacity among children and adolescents. Establishing healthy habits in childhood on the basis of the World Health Organization’s 2020 Physical Activity Guidelines is essential for proper physical, motor, and cognitive development.

**Objective:**

The primary aim of this study is to describe the level of physical activity (PA), sedentary behavior, and sleep of the child and adolescent population from 6 to 17 years of age in the Basque Autonomous Community (BAC). Our secondary aim is to establish a starting point for future research and intervention protocols to improve the existing reality.

**Methods:**

This cross-sectional study aims to recruit 1111 children and adolescents, aged 6 to 17 years from the BAC in a representative random sample. Participants will wear the ActiGraph WGT3X-BT triaxial accelerometer for 7 consecutive days in their nondominant wrist, and fill out a habit diary log of PA, mobility, and sleep routine. PA intensities, sedentary behavior, and sleep parameters (total bedtime, total sleep time, and sleep efficiency) will be calculated from raw accelerometer data using SPSS (IBM Corp). Participants will be randomly selected.

**Results:**

The results of this study intend to demonstrate significant differences in PA levels in different age and gender groups since the volume of school PA in the BAC decreases as the age of the schoolchildren increases. The total study sample includes 1111 participants. In April 2021, up to 50% of the sample size was reached, which is expected to increase to 100% by April 2022. This sample will allow us to analyze, discuss, compare, and assess the reality of the school population, in a sensitive period of adherence to behavior patterns, using data from the geographical and administrative area of the BAC. This study will provide a realistic insight into PA levels among children and adolescents in the BAC. It will also offer scientific contributions on the positive relationship between PA levels and sleep quality in this population.

**Conclusions:**

This study might highlight the need for the promotion of cross-sectional policies so that children and adolescents may increase their levels of PA, thus improving both the school environment and positive healthy behavior.

**Trial Registration:**

ISRCTN Registry ISRCTN65573865; https://www.isrctn.com/ISRCTN65573865

**International Registered Report Identifier (IRRID):**

DERR1-10.2196/31325

## Introduction

### Background

Physical inactivity (PI) and sedentary behavior are highly prevalent around the world and are associated with high morbidity and mortality [1]. In recent years, there has been an increase in the levels of sedentary lifestyle among the child and adolescent population, which is associated with lifestyle and has an impact on increasing obesity, diabetes, cardiovascular disease, cognitive capacities, and mental health [2,3].

In children and adolescents, physical activity (PA) improves physical fitness (both cardiorespiratory and muscular conditions), cardiometabolic health (blood pressure, dyslipidemia, obesity, glucose, and insulin resistance), bone health, cognitive ability (academic performance and executive function), and mental health (reducing symptoms of depression) [2,4,5].

The World Health Organization (WHO) recommends that children and adolescents between 5 and 17 years of age engage in at least an average of 60 minutes of PA per day, involving moderate to vigorous intensity (MVPA), mainly aerobic PA, with a minimum of 3 days a week of vigorous-intensity PA to limit sedentary behavior [2].

In Europe, approximately 80% of children and adolescents do not comply with the daily PA recommendations indicated by the WHO [6-8]. Hence, PI and sedentary lifestyle require intervention from an early age. If not, it may be too late as PA behaviors established in youth are maintained in adulthood [9]. It is estimated that in 2013, PI cost global health systems US $53.8 billion in direct health care, of which US $31.2 billion was allocated to the public sector, US $12.9 billion to the private sector, and US $9.7 billion for households [10]. However, it seems clear that intervention to promote PA must take place at an early age, since establishing habits and behavior changes are much easier and more achievable in childhood and adolescence than in adulthood [11].

In addition, PA is bidirectionally related to a shorter duration of sleep and an improvement in sleep efficiency, since PA contributes to an increase in sleep patterns [12]. Hence, physical exercise is already starting to be prescribed to improve sleep quality [13,14]. However, more national- and international-level studies are required among children and adolescents with objective measures to corroborate these findings [12].

Interventions promoting PA among children and adolescents must be supported by evidence that provides us the necessary information to do so efficiently. This study will allow us to analyze different realities (at different times, school settings, and ages), ultimately facilitating the design of policies and programs to promote PA and health on the basis of stated evidence [15]. Moreover, in the Basque Autonomous Community (BAC), there is a lack of evidence regarding the level of PA among children [16].

To determine the level of PA in the school population aged between 6 and 17 years in the BAC, and considering the benefits of PA for children and adolescents [17,18], this protocol aims to determine whether this group meets the established parameters of daily PA recommended by the WHO [2]. We hypothesize that >50% of the children do not meet the WHO recommendations, and that the level of PA in boys is greater than that in girls.

### Objectives

The main objective of this study is to describe the level of PA, sedentary behavior, and sleep of the child and adolescent population aged 6 to 17 years in the BAC.

The secondary objectives of this study are to (1) contribute to the theoretical, conceptual, and methodological development of research devoted to the study of healthy behavior and well-being of school-age children; (2) monitor and compare healthy behaviors and characteristics of the social contexts in which school-age children develop; (3) develop collaboration with organizations and associations to activate initiatives aimed at promoting health among the school population; (4) promote and support the creation of a network of local professionals to integrate active and healthy behaviors during childhood and adolescence; and (5) strengthen the international research network in the field of promoting PA among school-age children.

## Methods

### Methods Overview

This protocol shows potential in terms of collaborative, interorganizational, and collaborative work among the 3 Basque universities (Basque Country University, Mondragon University, and University of Deusto) along with 2 companies (Athlon Cooperative Society and Osasuna Mugimendua Kontrola Ltd). They are innovative and proactive in the field of PA program intervention for health among different groups and social strata, creating new educational programs at the universities as well as new socio-sanitary interventions prescribing PA for different populations. Thus, they work for transversal and interdepartmental support of the PA and sports, educational innovation, and public health departments of the Basque government.

### Participants and Selection Criteria

According to data extracted from the Basque Statistics Institute (EUSTAT) [19], as of October 16, 2020, the reference population to extract the sample residents in the BAC, aged between 6 and 17 years (born between 2003 and 2014), is 254,093 people, of whom 130,645 are boys and 123,448 are girls.

The corresponding sample size, considering that we are referencing a universal population greater than 100,000 people (referred as infinite for sample size calculation) is 1111 participants, at a confidence level of 2σ of 95.5%, an error limit of 3%, and heterogeneity of 50% [20]. To ensure a proportionate distribution of the sample in all age groups, territories, public and private centers, as well as girls and boys, these 1111 people were selected in accordance with the distribution detailed in Table 1. This sample is defined for all the assessment tests that comprise the project.

There is a proportional and random stratification based on province and county, age, gender, education network (public or private), and medea (socioeconomic level based on the deprivation index per census section, which enables the identification of sections with socioeconomic conditions), along with some inclusion and exclusion criteria that are listed in Textbox 1. Schools were selected randomly on the basis of the above-mentioned criteria.

**Table 1 table1:** Sample size and the current sample (N=1111).

Grade	Araba province				Bizkaia province				Gipuzkoa province				Total			
	Male		Female		Male		Female		Male		Female		Male		Female	
	Sample, n	Current sample, n	Sample, n	Current sample, n	Sample, n	Current sample, n	Sample, n	Current sample, n	Sample, n	Current sample, n	Sample, n	Current sample, n	Sample, n	Current sample, n	Sample, n	Current sample, n
First primary	8	9	7	8	22	6	21	6	14	1	14	1	44	16	43	15
Second primary	7	8	7	8	22	5	21	5	15	1	14	1	44	14	42	14
Third primary	8	8	7	7	23	5	22	5	16	1	15	1	48	14	44	13
Fourth primary	8	8	8	8	24	6	23	6	16	1	16	1	48	15	47	15
Fifth primary	8	6	8	7	24	6	23	6	17	0	16	1	49	12	47	14
Sixth primary	8	6	7	6	24	6	23	8	17	1	16	0	49	13	45	14
First secondary	8	7	7	6	25	4	24	5	17	0	16	1	50	11	47	12
Second secondary	7	6	7	6	25	4	22	5	17	1	16	0	48	11	46	11
Third secondary	7	8	7	7	24	4	22	10	17	0	16	1	48	12	45	18
Fourth secondary	7	8	7	8	24	10	23	8	17	1	16	0	47	19	45	16
First high school	7	8	7	7	24	8	23	14	16	1	16	1	48	17	45	22
Second high school	7	8	7	7	24	3	22	3	17	1	15	1	48	12	44	11
Total	90	90	86	85	285	67	269	81	196	9	186	9	571	166	540	175

Inclusion and exclusion criteria.

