**Exclusion criteria:**
Nonconsent or refusal by the child or adolescent to complete the physical activity diary or use the accelerometer, even with signed informed consent by their parents or legal guardiansPhysical or intellectual disability that prevents completing the daily physical activity or use of the accelerometer in accordance with the defined protocol. Each case will be assessed with each school’s teaching team and with the parents or legal guardians of the minor

To reach 1111 individuals, the sample unit selection will be conducted in multiple stages, so that a random sample of all age strata will be obtained, and a subsequent selection (by randomization) will be made to meet the needs of age, gender, and type of established center for the project. The recruitment process can be divided into three phases: contact with the center, contact with the families, and contact with the students. The contact with the centers is initiated via email or a telephone call. If the school shows interest, we arrange a meeting with the school’s principal. The principal selects a person from the school who then becomes the person in charge of the selection process and sending the information to the parents, usually the physical education teacher. Depending on the requirements of the total sample, the age ranges that need to be covered in each school are selected. During this phase, the physical education teachers of each center will be contacted, as well as the counselors for each grade level to request their collaboration and thus carry out an initial preselection of students to participate in the study (Figure 1). The information and the documents to be filled out are sent to the parents. A lottery is held among the participants who meet the requirements (age, gender, and others) and whose parents have given their consent. If the principal, the physical education teacher, the participants, or their parents have queries about the study, they are clarified. A day is set for placing the accelerometers on the selected participants, and after 7 full days they are removed.

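### The 3% error limit behind n = 1111 assumes a simple random sample, but pupils are drawn through schools; at 50% heterogeneity the limit fails if the net design effect exceeds 1

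*Protocol article*

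**What the plan says.** The Protocol article gives every input to its sample size in Participants and Selection Criteria. The reference population of 254,093 is a "universal population greater than 100,000 people (referred as infinite for sample size calculation"), and the required number "is 1111 participants, at a confidence level of 2σ of 95.5%, an error limit of 3%, and heterogeneity of 50" percent. No other input appears.

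The design is described in the same section: "There is a proportional and random stratification based on province and county, age, gender, education network (public or private), and medea", the last being a deprivation index. It adds: "Schools were selected randomly on the basis of the above-mentioned criteria". The recruitment text after the exclusion criteria says that "the sample unit selection will be conducted in multiple stages". Schools are approached, the age ranges needed from each school are fixed, and pupils are drawn by lottery from those whose parents have consented. A day is then set for fitting the accelerometers to the pupils selected.

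The article gives no number of schools, pupils per school, ICC or design effect.

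**The concern.** The formula treats the 1111 children as independent draws from the whole population. The described design takes groups of children from the same schools. Schoolmates share a timetable, physical education lessons and recess, which Study Variables lists among the settings in which activity is measured. They also share a fitting day, and so a measurement period. The Discussion expects pandemic restrictions in force at the time to affect the measurements, and pupils measured together share those too. Positive correlation within schools is therefore to be expected, and it lowers the information per child.

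The main objective is descriptive, and 3% at 95.5% confidence is the only precision the article states for its estimates. If that figure is read as the precision of this design, the prevalence estimates will look firmer than they are. This matters most if the proportion not meeting the World Health Organization recommendation lies near the 50% named in the Background hypothesis.

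**Working it through.** **Inputs from Participants and Selection Criteria:** z = 2, error e = 0.03, p = 0.50, population treated as infinite.

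**Step 1. Reproduce the plan's figure.**
n = z² p(1 − p) / e² = 4 × 0.25 / 0.0009 = 1111.1. The stated 1111 reproduces.

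Near variants do not give it:
- z = 1.96: 1067.1
- exact two-sided 95.5% multiplier: 1116.3
- z = 2 with finite population correction for 254,093: 1106.3

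So 1111 corresponds to z = 2, an infinite population and a design effect of 1. There is no reserve: at p = 0.50 the margin is already 3.00%.

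**Step 2. Add clustering by school.**
DEFF = 1 + (m − 1) × ICC
Margin = 2 × √(p(1 − p) × DEFF / n)

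The documents give neither m nor ICC, so the values below are assumptions. As a rough guide to m, Instrument says that 50 accelerometers were bought. All rows take n = 1111 pupils analysed and ignore any gain from stratification.

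| m | ICC | DEFF | Effective n | Margin, p = 0.50 | Margin, p = 0.20 |
|---|---|---|---|---|---|
| – | 0 | 1.00 | 1111 | ±3.00% | ±2.40% |
| 10 | 0.02 | 1.18 | 942 | ±3.26% | ±2.61% |
| 20 | 0.05 | 1.95 | 570 | ±4.19% | ±3.35% |
| 40 | 0.10 | 4.90 | 227 | ±6.64% | ±5.31% |

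Example, third row: DEFF = 1 + 19 × 0.05 = 1.95, and 2 × √(0.25 × 1.95 / 1111) = 0.0419.

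A wider grid, m from 10 to 50 and ICC from 0.01 to 0.10, gives margins from ±3.13% (DEFF 1.09) to ±7.29% (DEFF 5.90) at p = 0.50.

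**Step 3. Sensitivity to p.**
The Background cites about 80% non-compliance in Europe, that is p near 0.20 complying. Then 2 × √(0.16 / 1111) = 2.40%. The design effect at which the margin reaches 3% is 0.25 / 0.16 = 1.56.

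**The case against.** **The article is a condensed document.** An analysis that accounts for school may be set out in a statistical analysis plan that is not shown. That stands as far as the tests listed under Statistical Analysis go: their silence on clustering is not in itself a fault. It does not rescue the stated 3%, which the article derives in full from a formula that does not match the design.

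**Stratification could offset the loss.** The strata include county, school network and deprivation index, which may absorb part of the difference between schools. This stands as a limit on the size. The article claims no such gain, and nothing in it lets the gain be quantified, so the condition has to be put on the net design effect.

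**p = 0.50 is the worst case.** This also stands. Near p = 0.20 the mild case above is ±2.61%, inside 3%. Even the widest case in the table, ±5.31%, would leave an 80% non-compliance figure far from the 50% in the hypothesis.

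**Further readings a reader might infer, which the documents do not support:**
- *The arithmetic is wrong.* It is not; 1111 reproduces exactly.
- *The study certainly misses 3%.* That needs an ICC and a cluster size, which are not given.
- *Refusals and lost recordings were ignored.* Refusing the diary or device is an exclusion criterion, and Data Collection says the draw continues until each area and center has its required number. An allowance for unusable recordings is detail that an article commonly leaves to the full protocol.
- *The 3% is promised for sexes, grades or provinces.* The section ties it to the whole reference population and claims no subgroup precision.

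**Conclusion.** The point holds in a conditional form. The sample size rests on a design effect of exactly 1, while the design selects schools and then pupils within them. At the stated 50% heterogeneity, the 3% limit is therefore not delivered if the net design effect after stratification exceeds 1, which the shared school setting and measurement period make likely.

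The documents do not fix the size of the loss. Under the three assumed pairs of m and ICC the margin is about 3.3%, 4.2% and 6.6%. For an outcome with a proportion near 0.20, 3% could still be met under mild clustering.

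**What to change.** Keep 1111 and change four things:

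1. State that 3% applies to the proportion for the whole Basque Autonomous Community, under simple random sampling only.
2. Give the expected margin under the actual design as 2 × √(p(1 − p) × [1 + (m − 1) × ICC] / n) over a stated ICC range. Here m and n must be the pupils actually analysed, per school and in total, not the numbers planned.
3. Compute confidence intervals and tests with school-clustered or design-based standard errors. Restating the margin alone would not stop the results from being published with too narrow intervals. The center number is already part of the participant code (Data Collection), so no new data are needed.
4. If an ICC is estimated from the 341 children already measured, call it provisional. Table 1 shows only 18 of them (9 + 9) from Gipuzkoa, and the number of schools they come from is not given.

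The cost is revised wording and an analysis specification. The stated precision becomes less favorable. No extra participants or procedures are required.

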**Inclusion criteria:**
Belonging to the student body of a participating school or instituteHaving the authorization to participate through a signed informed consent form by the parents or legal guardians of the child or adolescent
**Exclusion criteria:**
Nonconsent or refusal by the child or adolescent to complete the physical activity diary or use the accelerometer, even with signed informed consent by their parents or legal guardiansPhysical or intellectual disability that prevents completing the daily physical activity or use of the accelerometer in accordance with the defined protocol. Each case will be assessed with each school’s teaching team and with the parents or legal guardians of the minor

To reach 1111 individuals, the sample unit selection will be conducted in multiple stages, so that a random sample of all age strata will be obtained, and a subsequent selection (by randomization) will be made to meet the needs of age, gender, and type of established center for the project. The recruitment process can be divided into three phases: contact with the center, contact with the families, and contact with the students. The contact with the centers is initiated via email or a telephone call. If the school shows interest, we arrange a meeting with the school’s principal. The principal selects a person from the school who then becomes the person in charge of the selection process and sending the information to the parents, usually the physical education teacher. Depending on the requirements of the total sample, the age ranges that need to be covered in each school are selected. During this phase, the physical education teachers of each center will be contacted, as well as the counselors for each grade level to request their collaboration and thus carry out an initial preselection of students to participate in the study (Figure 1). The information and the documents to be filled out are sent to the parents. A lottery is held among the participants who meet the requirements (age, gender, and others) and whose parents have given their consent. If the principal, the physical education teacher, the participants, or their parents have queries about the study, they are clarified. A day is set for placing the accelerometers on the selected participants, and after 7 full days they are removed.

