### Data Collection

Each participant will be identified by a unique and confidential numerical code, which is assigned after informed consent is obtained from the legal guardians. Those responsible for the database must save the files on servers with a password. To determine the codes, the following process is followed:

Province: 1=Araba, 2=Bizkaia, and 3=Gipuzkoa.Town (000)—each town is assigned a 3-digit number (eg, 001, 002, etc)Education center is assigned a 3-digit number (eg, 001, 002, etc).The academic stage between primary, secondary, or high school or secondary vocational training (1, 2, and 3)The gradeThe classroom in letters A, B, C, and DThe student number (00) considering that each classroom will have a maximum of 30 students.

Consequently, each participant will have a 12-digit code; for example, 2 022 060 11 D 07.

Prior to data collection, the study presentation brochure was emailed to the centers inviting them to participate, along with the informed consent document to authorize their children to participate in the study. Each center shares information about the study with the families through the established communication channel in each case (web platform or email), sending the legal guardians the information received at the center.

If families are interested in participating, they must send their informed consent to the head of the education center, and depending on the number of volunteers, a random draw will be held until the sample requirements established in each area and center are reached.

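### The abstract claims a representative random sample, but the pupil draw runs only among consenting volunteers after a staff preselection, so the 3% error limit does not cover selection

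*Protocol article*

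**What the plan says.** The Abstract (Methods) of the protocol article describes recruitment of 1111 children and adolescents "aged 6 to 17 years from the BAC in a representative random sample" and adds: "Participants will be randomly selected". Methods, Participants and Selection Criteria, reports proportional random stratification by province and county, age, gender, school network and deprivation index, with schools chosen at random on those criteria. The sample size is set "at a confidence level of 2σ of 95.5%, an error limit of 3%, and heterogeneity of 50" percent, for a reference population that "is 254,093 people, of whom 130,645 are boys and 123,448 are girls".

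The recruitment steps follow the exclusion criteria in the same section. A school goes forward if it shows interest. The principal names a person, usually the physical education (PE) teacher, to run the selection. PE teachers and grade counselors are asked for their help to "carry out an initial preselection of students to participate in the study". Documents go to parents. Only then: "A lottery is held among the participants who meet the requirements (age, gender, and others) and whose parents have given their consent".

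Methods, Data Collection, gives the same order. Interested families return consent to the school and, "depending on the number of volunteers, a random draw will be held until the sample requirements established in each area and center are reached".

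**The concern.** The main objective is descriptive: activity, sedentary behavior and sleep in all 6- to 17-year-olds of the region. The Introduction also hypothesizes that more than half do not meet the WHO recommendation. For such estimates, how pupils enter the sample is the main condition for validity.

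A lottery among consenters makes the sample random with respect to the consenters, not the school roll. The strata balance place, age, gender, school network and deprivation. They do not balance interest in activity or willingness to wear a monitor and keep a diary for a week, which may plausibly be related to the outcome. A larger sample would narrow the interval without changing this. A reader who takes the abstract at its word would read the 3% limit as the total uncertainty about the population, which it is not.

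**Working it through.** **1. The plan's own figure.** Inputs from Participants and Selection Criteria: z = 2, p = 0.5, e = 0.03, population treated as infinite.

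n = z² × p(1 − p) / e² = 4 × 0.25 / 0.0009 = 1111.1

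This reproduces 1111. A finite population correction with 254,093 gives 1106.3, so treating the population as infinite is harmless. The formula is for simple random sampling: its only error term is sampling error.

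**2. Claim and procedure, stage by stage.**

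| Stage | Claimed | Described procedure |
|---|---|---|
| Schools | Chosen at random within strata | Proceeds only if the school is interested |
| Preselection of pupils | None mentioned in the abstract | By PE teachers and counselors, criteria and mechanism not stated |
| Families | Not mentioned in the abstract | Consent returned before any draw |
| Draw | Participants selected at random | Among eligible pupils with consent, until quotas are filled |

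Two sections independently place the draw after consent, so this is not one loose sentence.

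**3. Can the effect be sized?** If r is the consenting fraction and d the difference between consenters and non-consenters in the share meeting the recommendation, bias = (1 − r) × d. The article gives neither r nor d, nor the sign of d. The figures below are assumptions only. Coverage is that of the ±3-point interval with SE = √(0.25/1111) = 0.015.

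| Assumed r | Assumed d (points) | Bias (points) | Coverage |
|---|---|---|---|
| 90% | 5 | 0.1 × 5 = 0.5 | 94% |
| 70% | 10 | 0.3 × 10 = 3.0 | 50% |
| 50% | 10 | 0.5 × 10 = 5.0 | 9% |
| 30% | 20 | 0.7 × 20 = 14.0 | about 0% |

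The range runs from negligible to dominant, so it shows only that the 3% limit is silent on this source of error.

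**4. What the formula does not measure.** It is ordinary non-consent bias. If pupils were drawn first and refusals replaced by the next on the list, the final sample would still consist of consenters. If the same families would consent either way, bias from non-consent is unchanged. A changed order removes staff discretion and makes refusals countable. The staff preselection has no number attached to it and cannot be given one from the article.

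**5. What remains to be recruited.** From Results and Table 1, 1111 − 341 = 770. By province, using the targets in Results:
- Bizkaia: 554 − (67 + 81) = 406
- Gipuzkoa: 382 − (9 + 9) = 364
- Araba: 175 − (90 + 85) = 0

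**The case against.** Parental consent is mandatory with minors, so every study of this kind observes only consenters. Randomness is not absent either: schools are said to be randomly chosen, the text mentions later selection by randomization, and there is a draw within strata. The preselection sentence follows one about choosing the age ranges each school must cover and refers to a figure that is not available here, so it may mean no more than identifying eligible grades or classes. A condensed article may leave refusal logs and weighting to a fuller document.

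Most of this stands and limits the point. It does not rescue the unqualified claim in the abstract, because the draw after consent is explicit in two places. The limitation named in the Discussion is COVID-19 and its effect on recruiting schools, not volunteer selection.

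Two stronger readings are tempting. One is that PE teachers will favor active pupils. The article gives no preselection criteria, so this is conjecture. The other is that the estimate is biased by some multiple of the 3% limit, and that drawing pupils first would remove the bias. Every input to such a figure would be assumed, benign values are as admissible as severe ones, and the reordering leaves non-consent untouched. Absence of non-response weights is not counted against the article.

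**Conclusion.** The point holds in a limited form. The pupil stage is a random draw among volunteers within strata, in schools randomly selected but willing, after a staff preselection with no stated random mechanism. That is less than the abstract claims. The figure of 1111 is correct as arithmetic, and its 3% limit describes sampling error under random sampling only. The size and direction of any selection bias are unknown: the article supplies no consent rate and no volunteer versus non-volunteer difference. The conclusion rests on the stated order of steps, not on any assumption about teachers' choices.

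**What to change.** **1. Wording.** In the Abstract (Methods), replace the claim with wording such as: *stratified sample of volunteers drawn at random within randomly selected, consenting schools*. State that the 3% limit covers sampling error only. Qualify the statements in the Abstract (Results) and the Discussion that the study will show activity levels realistically, and add volunteer selection to the limitations. The Conclusions do not contain the claim and need no change on this account. Cost: text only.

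**2. Remaining recruitment (770 of 1111).** Replace staff preselection with a random draw from the class roll in each required grade-by-sex cell. The school makes the draw with a random list supplied by the study, so that no identities leave the school before consent; at present, codes are assigned only after consent. Invite the drawn pupils, count refusals and replacements, and report participation by school and cell. This removes discretionary preselection and makes non-response measurable; it does not remove non-consent bias. Cost: some extra follow-up of invited families, and probably a notification to the ethics committee. If recruitment is already complete, only part 1 applies, together with a description of how preselection was done.

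**3. Before and after.** Flag the 341 already recruited and compare them with later recruits within province, to avoid confounding the change with region. Bizkaia (148 recruited, 406 to come) is the main source. Araba is essentially complete, and Gipuzkoa has only 18 so far.
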